## **13 Insurance**

All subjects will be insured by the Sponsor against injury caused by their participation in the study according to local legal requirements in Sweden where the study takes place.

## **14 Compensation of study participants**

Based on our model for economical compensation to study subjects, participants in study will be paid 2000 Swedish kronor for compensation of discomfort and time (taxable income).

Travelling expenses to study visits will be compensated according to the public transportation rate after the study.

## **Appendix I: Rome IV criteria**

### **Diagnostic criteria for Irritable Bowel Syndrome:**

Recurrent abdominal pain on average at least 1 day/week in the last 3 months, associated with two or more of the following criteria:

1. Related to defecation
2. Associated with a change in the frequency of stool
3. Associated with a change in the form (appearance) of stool

(These criteria should be fulfilled for the last 3 months with symptom onset at least 6 months prior to diagnosis.)

### **Diagnostic criteria for Irritable Bowel Syndrome with predominant diarrhoea:**

More than one-fourth (25%) of bowel movements with Bristol stool form types 6 or 7 and less than one-fourth (25%) of bowel movements with Bristol stool form types 1 or 2.

## Appendix II: Questionnaire on background information

Datum för undersökningsbesök 20 \_\_\_\_\_. \_\_\_\_\_. \_\_\_\_.

### Bakgrundsfakta om patienten

1. Kön                                      Man                      Kvinna

2. Födelsedatum                      19 \_\_\_\_\_. \_\_\_\_\_. \_\_\_\_.

3. Längd                                      \_\_\_\_\_, \_\_\_\_ cm

4. Vikt                                      \_\_\_\_\_, \_\_\_\_ kg

### 5. Vilken högsta utbildningsnivå har du?

1. Högstadium
2. År på gymnasium
3. Gymnasium
4. År på högskola
5. Examen på högskola
6. Annan utbildning, vilken? \_\_\_\_\_

### 6. Har läkare konstaterat att du har någon eller några av följande sjukdomar?

|                                          |     |    |
|------------------------------------------|-----|----|
| Hjärtsjukdom                             | Nej | Ja |
| Vilken hjärtsjukdom? _____               |     |    |
| Stroke                                   | Nej | Ja |
| Förhöjt blodtryck                        | Nej | Ja |
| Sockersjuka (diabetes)                   | Nej | Ja |
| Cancer                                   | Nej | Ja |
| Vilken cancer? _____                     |     |    |
| Smärtor i övre delen av buken (dyspepsi) | Nej | Ja |

|                              |     |    |
|------------------------------|-----|----|
| Laktosintolerans             | Nej | Ja |
| Celiaki                      | Nej | Ja |
| Annan mag- eller tarmsjukdom | Nej | Ja |
| Vilken tarmsjukdom? _____    |     |    |
| Osteoporos                   | Nej | Ja |
| Allergi (även födoämnes-)    | Nej | Ja |
| Vilken allergi? _____        |     |    |
| Psykisk sjukdom              | Nej | Ja |
| Annan långvarig sjukdom?     | Nej | Ja |
| Vilken sjukdom? _____        |     |    |

**7. Hur länge har du haft symptom på irriterad tarm?**

1. Mindre än 6 månader
2. 6-11 månader
3. 1-5 år
4. Mer än 5 år

**8. Äter du någon medicin regelbundet för behandling av irriterad tarm (t.ex. förstoppnings- och diarrémedicin, fiberpreparat)?**

Nej                      Ja

Om du har det, vilka mediciner/preparat (handelsnamn) och vilka doser (dos/frekvens) använder du?

---

---

**9. Äter du någon annan medicin regelbundet?**

Nej                      Ja

Om du har det, vilken (medicinens handelsnamn) och vilka doseringar (dos/frekvens)?

---

---

**10.När använde du senast antibiotika eller annan antimikrobisk medicin som intas genom munnen (svamp-, virus-, amöbamediciner)?**

Medicineringens slutdatum |\_ |\_. |\_ |\_. |\_ |\_

Medicinens namn, dosering (dos/dag):

---

**11. Har du gennemgået operationer i mag- eller tarmkanalsområdet?**

Nej Ja

Om det är så, vilka operationer och vilka år?

---

**12. Har du haft inflammationer i mag-tarmkanalen (t.ex salmonella, kampylobakterier) de senaste tre åren?**

Nej Ja

Om det är så, när och vad konstaterades vara orsaken till inflammationen?

---

Om det är så, har symptomen på irriterad tarm uppstått efter inflammationen?

Nej                      Ja                      Det kan jag inte svara på

**13. Har du haft konstaterad helikobakterieinfektion?**

Nej Ja

Om det är så, vilket år?

---

Om det är så, har man behandlat infektionen med antibiotika?

Nej Ja

Om man har det, har man med undersökningar försäkrat sig om att avhysningen av heliobakterien har lyckats efter avslutat vård?

Nej                      Ja

**14. Har du någon specialdiet (t.ex. laktosfri, glutenfri eller vegetarisk?)**

Nej                      Ja

Om du har det, vilken? \_\_\_\_\_

**15. Om du har konstaterad laktosintolerans, äter du då låglaktos (HYLA-och INTO-produkter) eller helt laktosfri kost?**

Nej                      Ja

**16. Om du har konstaterad laktosintolerans, använder du laktaspreparat som kan köpas på apotek?**

Regelbundet                      Sporadiskt                      Använder inte preparat

**17. Äter du pre- eller probiotiska preparat?**

Nej                      Ja

Om ja, vilka? \_\_\_\_\_

**18. Röker du?**

Nej                      Ja                      Sporadiskt

**19. Använder du snus?**

Nej                      Ja                      Sporadiskt

**20. Använder du alkohol?**

Dagligen    Varje vecka    Varje månad    Mer sällan/Använder inte alkohol

**För Kvinnor**

**21. Är du gravid eller ammar du?**

Nej                      Ja

## Appendix III: Food frequency questionnaire (FFQ)

(Screenshot example)

**For the type of food you eat at least once a month, choose in the drop down menu how often you eat them.**

*Only fill out what you usually eat.*

|                                                          | Times per day | Times per week | Times per month |
|----------------------------------------------------------|---------------|----------------|-----------------|
| White bread (eg tin loaf, loaf, flatbread)               | ...           | ...            | ...             |
| Whole grain bread (eg rye bread, whole meal bread, Rusk) | ...           | ...            | ...             |
| Crisp bread                                              | ...           | ...            | ...             |
| Processed sour milk, yoghurt, yoghurt drink, smoothie    | ...           | ...            | ...             |
| Muesli, cereals                                          | ...           | ...            | ...             |
| Oatmeal porridge                                         | ...           | ...            | ...             |
| Flaxseeds                                                | ...           | ...            | ...             |
| Hard cheese                                              | ...           | ...            | ...             |
| Bag cheese, dessert cheese (eg Philadelphia, brie)       | ...           | ...            | ...             |
| Marmalade, jam, apple purée, honey                       | ...           | ...            | ...             |
| Liver pâté                                               | ...           | ...            | ...             |
| Cold cuts (eg ham, salami)                               | ...           | ...            | ...             |
| Egg, omelete                                             | ...           | ...            | ...             |

<< >>

**You have mentioned that you eat bread. How many slices of bread do you usually eat each time?**

☐ 1-2 slices  
☐ 3-4 slices  
☐ 5-6 slices  
☐ 7 slices or more  
☐ Don't know/Don't want to answer

<< >>

## Appendix IV: 3-day food diary

### Instruktioner

Skriv ner allt du äter och dricker för tre hela dagar innan ditt besök.

Ange även vad klockan är när du börjar måltiden.

Skriv sedan ett livsmedel på varje rad, och beskriv maten och livsmedlen så noggrant du kan. Beskriv exempelvis vilken sorts mjölk, fil eller yoghurt du äter eller dricker, vilket sorts ost och vilken fetthalt den har, vad bröd sorten heter och annat. Ange gärna produktnamn eller märke på produkterna.

Beskriv också hur maten är tillagad. Är maten kokt, stekt, panerad, grillad eller gratinerad?

Glöm inte tillbehör till maten, såsom senap, lingonsylt, sås, mjölk eller socker i kaffe och te eller småsaker som äts mellan måltiderna som tabletter, frukt, kakor, saft.

När du lagar maten själv kan du skriva ner de ingredienser du använt. Om du äter mat någon annan lagat kan du försöka gissa vad vilka ingredienser som används och hur maten tillagats, eller fråga den som lagat den.

Mängder kan anges i gram (om det står på en förpackning), matskedar (msk), deciliter (dl) eller stycken (st). Använd det som är enklast för dig.

Ett tips kan vara att fotografera maten för att ytterligare dokumentera!

**Nedan följer ett exempel på hur intaget av mat kan dokumenteras.**

| Måltid        | Tid          | Livsmedel                    | Mängd
(dl/g/st) |
|---------------|--------------|------------------------------|--------------------|
| Middag | 19.00 | Pasta                 | 200 g       |
|               |              | Köttfärs fetthalt 12% | 150 g       |
|               |              | Tomatssås, dolmio     | 2 dl        |
|               |              | Permesan ost, 32 %    | 10 g        |
|               |              | Olivolja, ZETA        | 0,25 dl     |
|               |              |                              |                    |
|               |              | O,s,v....             |                    |
|               |              |                              |                    |

Studiekod: \_\_\_\_\_ Datum: \_\_\_\_\_

### Dag 1-3

[illegible]

## Appendix V: Diary about stool frequency and consistency

Nummer: \_\_\_\_\_ Startdatum: \_\_\_\_\_

Instruktioner: När det kommer avföring är det meningen att du fyller i siffror och bokstaven som motsvarar vad som hände för motsvarande datum och tidpunkt.

**Konsistens:** Fyll i typ 1-7 (se förklaring nedan)

**Känsla av ofullständig tarmtömning:** Om ja, fyll i K

**Exempel:** Måndag kl 10: 6, K

| Typ 1                                                                             | Typ 2                                                                             | Typ 3                                                                             | Typ 4                                                                             | Typ 5                                                                              | Typ 6                                                                               | Typ 7                                                                               |
|-----------------------------------------------------------------------------------|-----------------------------------------------------------------------------------|-----------------------------------------------------------------------------------|-----------------------------------------------------------------------------------|------------------------------------------------------------------------------------|-------------------------------------------------------------------------------------|-------------------------------------------------------------------------------------|
| Hårda klumpar, som nötter                                                         | Hård korv med klumpar i                                                           | Korv med sprickor på ytan                                                         | Korv, mjuk och slät                                                               | Mjuka bitar med tydliga kanter                                                     | Fluffiga bitar med otydliga kanter                                                  | Vattnigt, inga bitar                                                                |
| [figure not shown] | [figure not shown] | [figure not shown] | [figure not shown] | [figure not shown] | [figure not shown] | [figure not shown] |

|            | Måndag | Tisdag | Onsdag | Torsdag | Fredag | Lördag | Söndag |
|------------|--------|--------|--------|---------|--------|--------|--------|
| Datum →    |        |        |        |         |        |        |        |
| Tidpunkt ↓ |        |        |        |         |        |        |        |
| 06         |        |        |        |         |        |        |        |
| 07         |        |        |        |         |        |        |        |
| 08         |        |        |        |         |        |        |        |
| 09         |        |        |        |         |        |        |        |
| 10         |        |        |        |         |        |        |        |
| 11         |        |        |        |         |        |        |        |
| 12         |        |        |        |         |        |        |        |
| 13         |        |        |        |         |        |        |        |
| 14         |        |        |        |         |        |        |        |
| 15         |        |        |        |         |        |        |        |
| 16         |        |        |        |         |        |        |        |
| 17         |        |        |        |         |        |        |        |
| 18         |        |        |        |         |        |        |        |
| 19         |        |        |        |         |        |        |        |
| 20         |        |        |        |         |        |        |        |
| 21         |        |        |        |         |        |        |        |
| 22         |        |        |        |         |        |        |        |
| 23         |        |        |        |         |        |        |        |
| 24         |        |        |        |         |        |        |        |
| 01         |        |        |        |         |        |        |        |
| 02         |        |        |        |         |        |        |        |
| 03         |        |        |        |         |        |        |        |
| 04         |        |        |        |         |        |        |        |
| 05         |        |        |        |         |        |        |        |

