## 3 Study objectives

**The overarching aim** of this study is to investigate the effect of a 6-week intervention with two different probiotic products ((*Lactobacillus reuteri* ATCC PTA 6475 och Gastrus (*Lactobacillus reuteri* DSM 17938/ATCC PTA 6475)) on the intestinal permeability of diarrhoea-predominant IBS (IBS-D) patients.

**The primary endpoint** is the difference in small intestinal permeability, measured as the urinary lactulose/rhamnose secretion ratio, after a 6-week intervention with the probiotic products compared to the placebo product, in IBS-D patients.

**Secondary endpoints** are the differences between intervention with the probiotic products compared to the placebo in IBS-D patients on:

- The small intestinal permeability, measured as the urinary lactulose/rhamnose secretion ratio, after 3-week intervention
- Whole gut permeability measured as urinary sucralose/erythritol excretion ratio (0-24hrs) after 3 and 6 weeks
- Colonic permeability measured as urinary sucralose/erythritol ratio (5-24hrs) after 3 and 6 weeks
- Gastroduodenal permeability measured as urinary sucrose excretion (0-5hrs) after 3 and 6 weeks
- Various potential biomarkers of general intestinal barrier function and inflammation in blood and faecal samples after 3 and 6 weeks such as plasma i-FABP, faecal zonulin, serum zonulin, bacterial 16S ribosomal RNA (16S rRNA) gene copy number (whole blood), plasma vasoactive intestinal polypeptide (VIP), plasma high-sensitive C-reactive protein (hs-CRP), faecal calprotectin and plasma cytokines (e.g. IL-6 and IL-10)

**Exploratory endpoints** are the effects of the intervention with the probiotic products in comparison to the placebo in IBS-D patients on:

- Stool frequency and consistency (Daily diary on bowel movement using Bristol Stool Chart)
- Gastrointestinal symptoms as measured by the GSRS-IBS and IBS-SSS after 3 and 6 weeks
- Quality of life after 3 and 6 weeks (5Q-5D-5L, IBS-QOL)
- Perceived stress after 6 weeks (using the Perceived stress scale, PSS)
- Anxiety and depression symptoms after 3 and 6 weeks (HADS)
- Cortisol awakening rhythm (saliva) after 3 and 6 weeks
- Intestinal microbiota composition (16S rRNA-based next generation sequencing of faecal samples) after 3 and 6 weeks
- Metabolomic profile of faecal samples and blood, including SCFA metabolism and tryptophan catabolites such as 5-HT and melatonin, after 3 and 6 weeks.

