#### 4 Study design

This will be a single-centre, randomised, double-blinded, placebo-controlled intervention study with a parallel design and three study arms.

The study will investigate the effects of supplementation with the probiotic products *L. reuteri* ATCC PTA 6475 and Gastrus (*L. reuteri* DSM 17938/ATCC PTA 6475) on the intestinal barrier function, gut health and stress symptoms in diarrhoea-predominant IBS (IBS-D) patients. The test product is a tablet containing either ATCC PTA 6475 or Gastrus (DSM 17938/ATCC PTA 6475). The subjects will consume the product twice a day, giving a daily dose of  $1 \times 10^9$  CFU of each strain. The placebo product is an identical tablet except for the absence of probiotics. After having given their written informed consent, subjects will complete screening procedures to evaluate their eligibility for the study (visit 1). Study participants will undergo two baseline visits (visits 2 and 3, 3 weeks apart) to account for individual variations, and will then be randomly assigned to 6-week intake of either ATCC PTA 6475, Gastrus, or placebo in a ratio of 1:1:1 (stratified by sex). Participants will attend a study visit three weeks into the intervention (visit 4) and at the end of the intervention (visit 5, week 6). The intestinal permeability will be assessed using a standardized multi-sugar test at visit 2, visit 3, visit 4, and at end of intervention (visit 5). Blood, saliva and faecal samples will be collected at visit 2-5. In addition, gastrointestinal symptoms will be recorded at those visits (using GSRS-IBS, IBS-SSS). Quality of life using the 5Q-5D-5L and Hospital Anxiety and Depression Scale (HADS) scores will also be recorded at those visits. In addition, at visit 3 and visit 5, the IBS-QoL and the Perceived Stress Scale (PSS) will be completed. In a daily diary, participants will record stool frequency and consistency from visit 2 until end-of-study visit 5. Dietary habits of the patients will be assessed via a food frequency questionnaire (FFQ) and a 3-day food diary before the intervention (between visit 2 and 3).

During the entire run-in and intervention period, the subjects will be asked not to consume any probiotic products other than the study products. During the entire study subjects should maintain their habitual diet and life style such as physical activity level and sleep habits.

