### 6.4 Randomisation

Randomisation will be computerised by an independent researcher. A third party not otherwise involved in the study will label the active and placebo study products. Randomisation lists will be kept in sealed envelopes at the study sites and a sealed copy will also be kept at Sponsor site. The envelopes may not be open until all study data have been entered into the database and until the database has been locked. For exceptions, see “Serious Adverse Event” below. Randomisation will be stratified by gender. At screening, subjects will be assigned a screening number starting at 1001, according to their chronological entry into the study. As an example the first subject will have screening number 1001. If the subjects are suitable for study participation, they will receive their randomization number at Visit 1. Randomisation numbers will include the stratification number (Female = 5; Male = 9), and will be allocated sequentially in the order in which the subjects finalise Visit 1. For example, the first female included will receive the randomization number: 5001, whereas the fifth male included will receive the randomisation number: 9005.

Subjects will be asked to return the used packages from the Study Products to allow assessment by the investigator of compliance. The investigators will also assess compliance by a daily checklist distributed to the participants and by interviews at every visit.

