## **6.5 Symptom scales**

### **6.5.1 Daily diary about stool frequency and consistency**

The participants will complete a daily diary about their stool frequency and consistency based on the Bristol Stool Chart (Appendix V).

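### The Appendix V stool diary has no mark for a stool-free or completed day, so the denominator of the exploratory stool-frequency endpoint cannot be identified

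*Protocol*

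**What the plan says.** Protocol section 3 lists among the exploratory endpoints "Stool frequency and consistency (Daily diary on bowel movement using Bristol Stool Chart"), compared with placebo. Section 4 sets the recording period: "In a daily diary, participants will record stool frequency and consistency from visit 2 until end-of-study visit 5". By the visit schedule in Table 1 that runs from week -3 to week 6. Section 6.5.1 adds only that "The participants will complete a daily diary about their stool frequency and consistency based on the Bristol Stool Chart" and refers to Appendix V.

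Appendix V is the form itself, in Swedish. Its instruction makes a bowel movement the trigger for writing anything: "När det kommer avföring är det meningen att du fyller i siffror och bokstaven". The consistency code is "Fyll i typ 1-7 (se förklaring nedan"), and the letter K is added if evacuation felt incomplete. The grid has one column per weekday, a date row, and one row for each hour. It has no row, code or box for a day without stool and none for a day on which the diary was kept.

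One other daily record exists, in section 6.4: "The investigators will also assess compliance by a daily checklist distributed to the participants and by interviews at every visit". It concerns intake of the study product. Table 1 places the compliance diary in the intervention period only.

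**The concern.** A frequency needs a count and the time over which the count was observed. This form captures the count but not the observed time. A blank column may be a day with no stool, which should count as zero, or a day the participant forgot, which should count as missing. Nothing on the form separates the two. The date row does not settle it, because the form does not say whether a stool-free day is to be dated, and dates can be filled in beforehand.

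An analysis plan can choose a convention for blank days, but it cannot recover information that was never collected. That is why the point belongs to the form, which the protocol fixes. At stake is how far the stool-frequency values, and the size of any probiotic-placebo difference in them, can be trusted.

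**Working it through.** The protocol states no stool frequency, denominator or diary completeness, so there is no figure of its own to reproduce. What follows is an illustration on assumed inputs.

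**Inputs**
- Recording period: 9 weeks (section 4 and Table 1), 9 × 7 = 63 days, of which 6 × 7 = 42 are in the intervention.
- True mean μ: assumed 3.0 stools per day.
- Share of kept days that are truly stool-free, z: assumed 0-20%.
- Share of days on which the diary is not kept, m: assumed 0-20%, unrelated to the number of stools that day.

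**Formulas**
- Blank counted as zero (calendar days): expected rate = μ × (1 − m), whatever z is.
- Blank dropped (days with an entry): expected rate = μ / (1 − z), whatever m is.
- With a daily tick (completed days): expected rate = μ, for any z and m.

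**Results at μ = 3.0**

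| Convention | Share | Rate | Bias |
|---|---|---|---|
| Blank = zero | m = 0% | 3.00 | 0% |
| | m = 5% | 2.85 | −5% |
| | m = 10% | 2.70 | −10% |
| | m = 20% | 2.40 | −20% |
| Blank dropped | z = 0% | 3.00 | 0% |
| | z = 2% | 3.06 | +2.0% |
| | z = 5% | 3.16 | +5.3% |
| | z = 10% | 3.33 | +11.1% |
| | z = 20% | 3.75 | +25.0% |

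**Between arms, true means 3 and 2 (difference 1.0)**
- Calendar days, m = 15% in both arms: 3 × 0.85 = 2.55 and 2 × 0.85 = 1.70. The difference is 0.85; the ratio stays at 1.5.
- Entry days, Poisson counts: z = exp(−3) = 5.0% and exp(−2) = 13.5%, giving 3.16 and 2.31. The difference is 0.84.
- Entry days, z = 10% in both arms instead: 3.33 and 2.22. The difference is 1.11, so it is now inflated.

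The direction of the distortion under the second convention therefore depends on how z relates to the mean.

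**No true difference, both means 3**
- Same m in both arms: both rates fall alike and the difference is 0.
- m = 5% against 15%, calendar days: 2.85 against 2.55, a spurious 0.30 stools per day.
- Entry days: the rate does not depend on m, so unequal completion alone creates no difference.

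**The case against.** The strongest reply has four parts.

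**Blank days may be few.** These patients have predominant diarrhoea, so stool-free days may be rare, and if z is near zero the entry-day rate is nearly right. This stands as a possibility. The document does not establish it: Appendix I defines the subtype by stool form and not by a daily count, and section 7 allows antidiarrhoeal medication.

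**Power hardly changes.** A scaled-down mean brings a scaled-down standard deviation. In a simulation with gamma-Poisson counts (means 3 and 2, between-patient coefficient of variation 0.5, 42 days, 15% missed days, 25 per arm, Mann-Whitney test), either convention lowers the standardised difference by only 0.01-0.02 and power by one to two percentage points from about 74%. This stands. The harm lies in the size and meaning of the estimate much more than in the test.

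**Both rates can be reported.** For each patient, and so for each arm, the calendar-day and entry-day rates bracket the rate over days actually kept. This is true within an arm, but it is a weak repair for the contrast. In the Poisson example above the two conventions give differences of 0.85 and 0.84, and the true 1.0 lies outside both. A bracket that is sure to hold runs from 2.55 − 2.31 = 0.24 to 3.16 − 1.70 = 1.46.

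**The blank-day rule belongs in the SAP.** Agreed. Section 12 refers to an SAP, which is not shown, and the absence of a written denominator from the protocol is not counted here. Only the missing mark on the form is.

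A reader might also infer that every possible denominator is wrong, that the treatment difference always shrinks, or that a fall in diary keeping from run-in to treatment would by itself look like benefit. The document supports none of these. Each convention has a case in which it is exact. Shrinkage under both depends on an assumed count model. The comparison is with a randomised, double-blind placebo arm, so a fall-off common to the arms cancels when there is no true effect. Nothing in the protocol gives a reason to expect completion to differ by arm.

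**Conclusion.** The point holds as a minor weakness of the data-collection form. A blank diary day cannot be told from a stool-free day, so the stool-frequency denominator is not identifiable. That is less than saying it is necessarily wrong. Within the assumed shares, rates may be 5-20% too low or 2-25% too high, depending on the convention. The protocol gives neither share, and the figures assume that days are missed independently of stool count. The arm comparison is distorted mainly in scale. With no true difference in stool pattern, a false effect arises only if completion differs by arm, and then under the calendar-day convention.

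The reach is narrow: the frequency half of one of eight exploratory endpoints. The lactulose/rhamnose endpoint, the sample size in section 5.1 and consistency summaries per stool, such as the proportion of types 6-7, need no day denominator and are untouched.

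**What to change.** Before data collection, add one row to the Appendix V grid, to be ticked every day as either *no stool today* or *diary completed today*. Stool frequency can then be computed as recorded stools divided by completed diary days: ticked stool-free days count as zero, and days with neither an entry nor a tick are treated as missing. In the model above this removes the bias for any z and m, provided days are missed at random.

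The cost is one row on a paper form and one tick a day for the participant, with no extra visits or patients. The limit is that stools forgotten on a ticked day remain undetected. The change cannot be applied to days already recorded.
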